### Ethical Considerations

The Regional Committee of Research and Ethics in Western Norway (no. 599832) approved the design and procedures of this study. The ethical principles for research in the social sciences and the humanities will follow the Helsinki Declaration guidelines' [65]. From the start, participants’ needs will prevail over research interests. The agreement to participate in the study and an explicit written informed consent will precede data collection. Participants will be informed about all the relevant aspects of the study (eg, aims, methods, allocation, etc). They will also be reassured that their participation is voluntary and that they can withdraw at any time without detriment. The participant’s privacy and confidentiality will be assured throughout all research phases. Both researchers and psychologists will monitor potential adverse effects or special circumstances that will require participants’ removal from SEIB. Additionally, all participants can make use of care as usual, which seems particularly significant to those in the control condition who are waiting for the delayed SEIB program.

The participant’s informed consent will be obtained shortly after the death. However, several researchers have underlined the difference between being distressed, and not being capable of making decisions around enrollment in a bereavement research study [66,67]. In fact, bereaved people are often involved in complex decision-makings concerning the funeral planning, their financial situation, and so on. Besides, they do not report their research participation as undue strain [68]. Acknowledging a temporary distress, they emphasize their research participation as positive, without showing regrets, and highlight the benefits of participation when they are being respectfully, sensitively and properly cared for [68]. Nevertheless, given the closeness of T1 to the death, where the families may be acute distressed/disturbed, it is necessary to limit the potential strain that can be added to the families. Presenting many questions to the family members at this early time following the loss may lead to problems or even discourage their retention in the study. In addition, their diminished cognitive resources may negatively affect their ability to properly fill in many questionnaires at this time. Therefore, T1 will just comprise the use of the above -mentioned 2 questionnaires.

### Project Organization

This is a one-center study conducted in Norway for a timeframe of 3 years. It was initiated in November 2014 and will be completed by November 2017. An expert advisory board with representatives from (inter)national universities and institutions with special competencies in the grief/trauma field will provide on the study during the research process. This is of primary importance as there are few international (and none Norwegian) studies informing early follow -up practices following loss and trauma.

## Results

The present pilot study is ongoing and started enrolment of families in August 2015. Data collection is expected to be completed in June 2017.

## Discussion

### Implications of the Study

This pilot study will evaluate the plausibility and practicability of a future main trial. Furthermore, it will explore the preliminary short -term effects of an early multidimensional program designed to promote families’ grieving process and adjustment after a sudden death of a partner/parent, and to decrease the risk for complicated grief in both bereaved children and their surviving parents. The rationale for this study is embedded in the existing literature [26-28], our clinical experience, and the wishes for immediate assistance, outreach help, and help for their children expressed by the bereaved themselves [22,29].

### Strengths and Limitations

To our knowledge, this is the first study proposing an early preventive program that starts up in the first days following loss with the potential to adapt the intervention to the needs of bereaved families over time. It is also one of the first trials employing the delayed intervention design in the grief field in order to explore the effect of time on outcome variables. Therefore, this study will provide preliminary knowledge about the value of very early intervention following bereavement, which crucially calls for empirical support and clarification. In addition, the delayed intervention design overcomes some important ethical, methodological, and logistical constraints, because it assures intervention for all participants [69]. On the one hand, it seems to suit the needs of the families, who may show a strong wish for immediate assistance [22,29]. On the other hand, it can minimize possible dropout effects as our former experience in conducting research makes us believe that these families are likely to show a high expectation of receiving intervention from us. Accordingly, the delayed intervention design minimizes possible disappointment effects of those who are not allocated to their treatment choice, preventing the risk of refusing randomization [70]. As a result, we consider that the use of the delayed intervention design will maximize recruitment and retention. Consequently, considering that the lack of evidence of preventive interventions for bereaved has been linked to higher levels of complexity in implementing these studies [30], we think this delayed intervention design takes into account the interests of our bereaved families, promoting the study’s integrity, its effective implementation, and full potential.

Nonetheless, this pilot study may entail a number of possible limitations. First, recruitment constraints may lead to a small and/or possibly selective sample. The Norwegian population is small and our recruitment potential is not large, given that we need to wait for the potential traumatic event to happen. Besides, the intervention takes place at our center, which means we can only recruit in the surrounding county. Further, the bereaved families are contacted at the first time they meet health care personnel following the death, which may be particular demanding for some families, undermining their willingness to participate in the study.

Second, both early-SEIB and delayed-SEIB intervention groups can make use of care as usual, which may lead to carry -over effects [71]. This refers to the first support and help these families can receive from the crisis team, general practitioner, hospital, church, and/or school in the community. In communities outside the urban area, and in recruiting hospital wards, care as usual will vary greatly. However, families receiving other concurrent psychotherapeutic intervention will be excluded from the study and the Help Questionnaire may help to monitor some of these potential carry -over effects.

Third, a longer follow -up assessment should have been considered, as it would allow us to report on possible long -term effects, and to explore the sustainability of change over time [72]. Financial unfeasibility is the main reason that hinders the likelihood of looking at possible SEIB's long -term effects. Grant providers should recognize bereaved people as a particularly vulnerable, sensitive, and 'hard -to -reach' group that requires additional resources, both financial and from the research team.

Fourth, family participation may entail a small burden because it involves the fulfillment of a set of questionnaires at 4 time-points. The expected distress in relation to filling in questionnaires is anticipated to be highest at T1, because it takes place in the near aftermath of the death where families may be stunned or shocked. We try to minimize this burden by using 2 questionnaires at T1 (with an estimate short time to complete them: 15 to maximum 30 minutes), and having a researcher present with the families to provide help and assistance with the task. Besides, previous research have showed that the burden of filling in questionnaires was outweighed by the meaningfulness of participation, as it tends to increase families’ understanding of their grief reactions [68]. The intervention will take 1 to 2 hours per session and will require that the families express what help they think they need. Considering the needs of suddenly bereaved families, SEIB will hopefully operate as a protective factor, promoting individual and family’s adjustment. This is likely to stimulate a safer and less stressful mourning environment, which may even help to prevent further maladaptive trajectories. Therefore, we consider that the benefits for the individual and the family exceed the minimal constraints that this study may entail.

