In view of these detrimental influences of bereavement-related psychological distress on both the individual and the family system, it is crucial to break this cascade of negative cycles. It highlights the need of developing effective interventions aimed to promote resilience for both bereaved parents and their children, especially in the early stages that follow death [26,27] where the disabling consequences have been more strongly noticed [3]. Several clinicians and researchers in the loss and trauma field have emphasized the usefulness of early crisis intervention [26-28]. They argue that early intervention favors the attenuation of the initial dysfunctional appraisals and enables a better case management, and maximizes the chances of a more adaptive developmental pathway [27]. Norwegian studies on the users’ perspectives show that traumatic bereaved participants ask for: (1) immediate assistance, (2) outreach help, (3) help for their children, (4) information about the event and potential reactions, (5) possibility to meet with others who experienced similar situations, and (6) help over time [22,29]. Nevertheless, meta-analytic findings failed to show a significant effect of preventive approaches, pinpointing diverse methodological limitations among the studies [30]. To our knowledge, none of these studies assesses interventions taking place immediately after the loss. The start of these preventive programs ranges from 2 to 6 months post loss [31,32]. Thus, it is essential to develop well-designed randomized controlled studies [33] attempting to increase understanding about the best time to provide early intervention.

In line with this, the Systematic Early Intervention for Bereaved (SEIB) was developed. It is the first Norwegian program that proposes professional family assistance starting in the first days after a sudden and traumatic loss. Within a family perspective, SEIB seeks to facilitate natural mourning, resolve grief complications, promote parental capacity, and help the bereaved partner and their children to develop or enhance satisfying relations/activities, and to regain control over their life. The basis of this approach is from the field of early crisis intervention [26-28]. The existing literature [3,25], the wishes for help as expressed by the bereaved themselves [22,29], and our extensive clinical practice, are at the heart of this approach.

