## Methods

### Trial Design

As outlined in Figure 1, this study is a one-center, pilot, randomized controlled trial (RCT) with a delayed intervention design in which suddenly bereaved families will be randomly assigned to: the immediate-SEIB intervention group (receiving SEIB in the aftermath of the loss) or the delayed-SEIB intervention group (control condition; receiving SEIB 3 months post loss). Both groups can make use of care as usual from their communities.

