Session 3 takes place within 5 to 7 weeks post loss. The initial aim of this session is to address and process trauma aspects of the loss. Family members go through what they knew and thought about what happened, as well as their sensory experiences and body reactions at the time (especially the most difficult ones). If trauma-related problems persist, such as intrusive memories or thoughts, trauma focused methods such as Eye Movement Desensitization and Reprocessing (EMDR) [38] and Thought Field Therapy (TFT) [39] can be applied. The family members are advised to imagine having a conversation or write to the deceased and say goodbye (eg, writing a letter to the loved one, mentioning what they did not have time to say/do; ask for forgiveness if there are any regrets) [40]. A discussion around the balance between maintaining a constructive bond with the dead and keeping the lost one too close is also addressed. In addition, an emphasis is placed on living with grief over time, principally for the next coming months (eg, resume normal activities, interact with the environment, organize/tidying the dead person’s belongings, set goals for the family, use self-help techniques with videos found on the Internet). Finally, parents receive information for learning more about children’s reactions [41].

#### Session 4

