The rationale for both immediate-SEIB and delayed-SEIB versions relies on the need to minimize the initial misconceptions and maladaptive appraisals that may emerge in the aftermath of a traumatic event and that may exacerbate the onset of posttraumatic symptoms and complicated grief [27]. As a result, both immediate-SEIB and delayed-SEIB seek to enhance more appropriate coping responses that are expected to have an increasing effect over time. Also, early intervention may foster an open family climate that help the family to share facts and make decisions (eg, participating in rituals, school/work reentrance), favorable for them in a long-term perspective [27]. Traumatized parents tend to shield their children from facts, thus it seems important to stimulate proper levels of family communication, emotional expressiveness, and cohesion within the first weeks after a crisis event. This may decrease the individual and family arousal, increase family resilience, and stimulate a safer environment for trauma recovery [26]. These arguments constitute the base for our immediate-SEIB intervention and are in line with our clinical and research experience, showing bereaved people ask for immediate assistance [22,29]. The immediate-SEIB first follow-up period (session 4) is consistent with the International Classification of Diseases, suggesting that complicated grief meets its diagnostic criteria when the symptoms persist beyond 6 months after the death [43]. The immediate-SEIB second follow-up period (session 5) is consistent with the Diagnostic and Statistical Manual of Mental Disorders, requiring a minimum of 12 months [44].

The delayed-SEIB proposal is informed by the literature, given most preventive studies tend to start intervention within 2 to 6 months post loss [31,32]. For the delayed-SEIB intervention group, the first 3 sessions contain less advice on the acute handling of the situation (including children in rituals, return to work and school, securing social support) and less focus on reducing bodily activation by calming family members. They prioritize the traumatic aspects surrounding the death, and psychoeducation is adjusted to the reactions usually seen at this time-point (~3 months following the loss), when the unreality has abated and the social network is often less active in their support.

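### The immediate and delayed versions differ in content as well as start time, so the aim 6 contrast cannot isolate the effect of time that the Discussion claims for the design

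*Protocol article*

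**What the plan says.** The Discussion (Strengths and Limitations) counts the trial among the first "employing the delayed intervention design in the grief field in order to explore the effect of time on outcome variables". The Introduction sets the background: it calls for randomised studies "attempting to increase understanding about the best time to provide early intervention".

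Under Trial Design, one arm starts SEIB in the aftermath of the loss and the other is "the delayed-SEIB intervention group (control condition; receiving SEIB 3 months post loss".

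The Intervention section then describes a second difference: "For the delayed-SEIB intervention group, the first 3 sessions contain less advice on the acute handling of the situation", together with "less focus on reducing bodily activation by calming family members". It goes on: "They prioritize the traumatic aspects surrounding the death, and psychoeducation is adjusted to the reactions usually seen at this time-point". In the session-by-session outline, session 1 opens with calming and stabilising and session 2 with the sharing of facts. Of session 3 it says: "The initial aim of this session is to address and process trauma aspects of the loss".

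Aim 6 in the Introduction, the Objective in the Abstract and the analysis section all describe a comparison of an immediate with a delayed version of SEIB. The analysis sets the immediate group at T2 and T3 against the delayed group at T3 and T4. The limitations cover recruitment, care as usual, short follow-up and questionnaire burden. They do not mention that content differs between the arms.

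**The concern.** A delayed-start design speaks to start time alone only if what is started is the same in both arms. Here the programme changes with the start date. The change touches trauma work, and traumatic stress symptoms in parents and children (IES-R and CRIES-8) are the anticipated primary outcome. If the versions differ on these scales, the difference could come from starting earlier or later, from the different emphasis of the first three sessions, or from both.

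The pilot is meant to shape a main trial. If its aim 6 effect sizes are read as effects of time, a main trial could be planned as a test of timing around a contrast that does not identify timing.

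**Working it through.** The document gives no figure to reproduce, and no numerical effect can be computed from it. The check is one of identification.

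**Step 1. What differs between the arms by plan.**

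| Feature | Immediate version | Delayed version |
|---|---|---|
| Start | Aftermath of the loss, no later than 3 weeks | About 3 months after the loss |
| Acute advice (rituals, work and school, support) | Included | Less of it in sessions 1 to 3 |
| Calming and arousal reduction | Opening aim of session 1 | Less focus in sessions 1 to 3 |
| Traumatic aspects of the death | Opening aim of session 3; reminders and intrusive material also taken up in session 2 | Given priority in sessions 1 to 3 |
| Psychoeducation | Geared to the first weeks | Adjusted to reactions at about 3 months |

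The outline of sessions 1 to 3 is read here as the immediate version, because its session dates run from the first days to 7 weeks after the loss.

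**Step 2. What the planned contrast contains.** Let μ(s, c, t) be the mean outcome with start s (0 = immediate, 3 = about 3 months), content c (A = immediate version, D = delayed version) and t months of follow-up. Baseline lies within 3 weeks of the death, so t is close to time since loss. The first planned pair is immediate at T2 (t = 3) against delayed at T3 (t = 6):

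μ(0, A, 3) − μ(3, D, 6) = [μ(0, A, 3) − μ(0, A, 6)] + [μ(0, A, 6) − μ(3, A, 6)] + [μ(3, A, 6) − μ(3, D, 6)]

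The three brackets are, in order, elapsed time, start time and content. The second pair, T3 against T4, splits in the same way with t = 6 and t = 9. The gap in time since loss is 6 − 3 = 3 months in the first pair and 9 − 6 = 3 months in the second.

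**Step 3. Which terms the design can recover.** Both groups are assessed at T3 and T4. A comparison at equal follow-up would therefore remove the first bracket and leave start time plus content. To separate these two, one needs μ(3, A, t), the immediate content started at about 3 months. No arm provides it. Sample size does not help, because the quantity is never observed.

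**Step 4. Which comparison is unaffected.** Aim 5 compares immediate SEIB with the delayed group at T2, when the analysis section describes that group as receiving care as usual. The content D does not enter this contrast.

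**The case against.** The strongest reply is that the aims are already worded correctly. Aim 6, the Abstract and the analysis section compare versions, the Intervention section discloses the content difference and gives a reason for it, and nothing in the aims or analysis attributes a difference to start time alone. This stands. It leaves the Discussion sentence as the outlier, together with a limitation that is not listed.

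A second reply is that some of the reduced content belongs to the first weeks and that adapting it is part of starting later. A randomised comparison of two timing strategies, each with content suited to its moment, is legitimate. This also stands, but such a comparison estimates the effect of the package. It does not support a statement about time as such.

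A third reply is that this is a descriptive pilot not meant to test effectiveness. That lowers the stakes without removing the point, because the pilot is to inform the main trial.

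Four stronger readings are tempting, and the document does not support them:

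- A reader might infer that the trial can say nothing about the value of very early intervention. Aim 5 addresses that value and is not affected.
- A reader might infer from the Introduction that the trial promises to identify the best start time. That sentence describes a need of the field, and none of the six aims makes this promise.
- A reader might infer that trauma work fills one of three sessions in one arm and all three in the other. The outline gives opening aims, not amounts, and session 2 also touches on traumatic material.
- A reader might want to size or sign the bias. The amount of trauma work per arm and the dates of the delayed sessions relative to T3 are not in the text.

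**Conclusion.** The point holds in a limited form. The Discussion credits the design with a property it does not have. The aim 6 contrast identifies the joint effect of start time and session content and, as paired in the analysis, also a difference of 3 months since the loss. Randomisation still supports a comparison of the two packages, and aim 5 stands as planned.

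The size of the content effect is unknown and so is its direction. The conclusion rests only on the stated content difference and on there being two arms. It needs no assumption about how much the changed content matters, only that an effect of it cannot be ruled out. The consequence is for interpretation: what may be concluded from aim 6, and what a main trial may build on it.

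**What to change.** 1. Reword the sentence in Strengths and Limitations to say that the design compares two programme versions that differ in start time and in the content of the first three sessions.
2. State with aim 6, and add to the limitations, that no difference between the versions will be attributed to start time alone. Mention there that the T2/T3 against T3/T4 pairing also differs by 3 months since the loss.
3. Report beside the aim 6 effect sizes, by arm and up to each assessment, the number of sessions attended and whether trauma-focused methods were used. Attendance is already to be reported by the psychologists. The session logs are described as short, semistructured notes of impressions, so use of methods may not be recorded. If it is not, a tick-box in the therapist log is enough.

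No change to session content, sample or assessments is proposed. The cost is some rewording, a small table and possibly one added log field. The price in substance is a more modest conclusion about timing.

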### Conclusion

In sum, rather than evaluating SEIB efficacy or effectiveness, the current pilot study assesses the feasibility of a fully-powered trial. This study encompasses 3 major strengths that are the development of SEIB, the sample of bereaved families at considerable risk for complicated grief, and the use of the RCT with a delayed intervention design. It will possibly expand knowledge on the usefulness of a proactive, holistic, and supportive approach that may be of major importance for public mental health services, governments, and crisis teams.

